### Study population

The study will be conducted at the Orthopedic Department of UMCG. Inclusion criteria for the intervention group are:

– Use of CAS during rTKA.

– Minimum age of 18 years.

– Total revisions, re-implantations and partial revisions of either the tibial or the femoral part are included. For partial revisions, only measurements of the part of the prosthesis to be revised will be used.

Inclusion criteria for the historical control group are:

– rTKA without the use of CAS.

– Minimum age of 18 years.

– Total revisions, re-implantations and partial revisions of either the tibial or the femoral part are included. For partial revisions, only measurements of the part of the prosthesis that was revised will be used.

– Patients will be included if the NexGen® revision system (Zimmer Inc., Warsaw, Indiana, USA) was used.

Exclusion criteria for both groups are:

– Insert replacements and placement of a patellar button only.

– Patients who receive a tumor prosthesis during rTKA.

– Patients with a limited knowledge of the Dutch language or who are mentally incapable of participating.

In both the intervention group and the historical control group the anesthetic, analgesic and postoperative physiotherapy protocols are identical.

### Surgical procedure rTKA

rTKA can be described in three steps: 1) removal of implant, 2) classification of defects and 3) rebuilding of joint by “tibia first technique”. The first step is to extract the failing components and to remove all debris to create a new situation. Hereby bone will be preserved as much as possible, although bone of poor quality has to be removed.

The second step is to classify the bone defects according to the Anderson Orthopaedic Research Institute (AORI) [27]. In defect types 2a, 2b and 3 bone loss will be compensated by metal augmentations, while stems attached to the tibial and femoral components will spread the load to the implant interfaces to secure fixation.

The third step is the rebuilding of the knee joint with a revision prosthesis. The NexGen® revision system (Zimmer Inc., Warsaw, Indiana, USA), is used at the Department of Orthopedics of UMCG. Depending on the bone defects the NexGen Legacy Condylar Constraint Knee® (LCCK) (type 2a or 2b) or the NexGen Rotating Hinge Knee® (RHK) (type 3) is used. Tibial and femoral revision components are placed with press-fit stems, and if needed with augmentation blocks or trabecular metal cones. The revision prosthesis is fixed with bone cement (Refobacin® revision bone cement with clindamycin and gentamicin, Biomet Inc., Warsaw, Indiana, USA). Depending on the stability and integrity of the collateral ligaments, the type of articulating surface is chosen during surgery. With good collateral ligaments a posterior stabilizing component (Legacy Posterior Stabilized®, LPS) will give sufficient stability. However, in case of coronal plane instability a semi-constraint insert (LCCK) with a high post is needed. With gross collateral deficiency and multidirectional instability a rotational hinge is the best choice (RHK).

### Intervention group

In the intervention group, CAS will be applied during rTKA. The ORTHOsoft Navitrack® navigation system (Zimmer Inc., Warsaw, Indiana, USA) will be used. The navigation is based on an infrared reflecting system with use of trackers in the femur and tibia. The system guides the surgery by an image-free model based on anatomical landmarks identified by the surgeon. After the exposure a femoral tracker is placed proximally from the knee in the same knee wound or in an additional 3-cm incision. The tibial tracker will be placed in an additional 3-cm incision above the ankle. Before removal of the primary prosthesis, the navigation protocol is applied in which the anatomical landmarks are chosen and the system will build its model from the patient’s data. Thus, all anatomical landmarks are identified with the primary prosthesis in situ. The mechanical axis of the lower limb as measured with this system is the angle between the mechanical axis of the femur and tibia. The mechanical axis of the femur is the axis between the center of the femoral head and the deepest point of the intercondylar notch. The center of the femoral head is determined by moving the leg in a conical pattern, digitizing 14 distinct positions of the femoral tracker. The deepest point of the intercondylar notch is marked by the orthopedic surgeon. The mechanical axis of the tibia is the axis between the entry point of the proximal medullary canal and the center of the ankle. The entry point of the medullary canal is marked by the orthopaedic surgeon and the center of the ankle is assessed by marking the medial and lateral malleoli. Coronal and sagittal prosthesis alignment of the femoral and tibial components are calculated according to respectively the femoral and tibial mechanical axis. Rotation of the femoral component is determined according to the epicondylar axis. The orthopaedic surgeon marks the medial and lateral epicondyle and thus this axis is generated. Rotation of the tibial component is assessed in relation to the axis between the middle of the posterior cruciate ligament insertion and the medial third of the tibial tuberosity. Both landmarks are marked by the orthopaedic surgeon. The navigation system will guide the surgery in positioning the components and choosing the size of the implants.

When implanting a press-fit stem, it may be that alignment of the components are influenced by the stem. After removal of the primary prosthesis and preparation of the bone cuts, different provisional components are tried in order to determine the correct type and size of the components. In this way, and by checking the alignment of the components with the navigation system, the orthopaedic surgeon will know if the stem influences the component alignment. In the revision system we have the availability of straight stems and off-set stems to use the best position of the component in combination with the stem but not forced by the stem. When this is the case, a stem of a smaller diameter will be chosen, so that the components are placed according to the bone cut made using the navigation system instead of the stem. Cementing underneath the tibial tray and leaving the stem uncemented generally provides enough component stability. In the rare case of the components not being rotationally stable, the stem will be cemented.

### Historical control group

In the control group the position of the revision prosthesis was determined using mechanical intramedullary alignment guides for the femur and tibia. Positioning of the components and sizing were based on the same anatomical landmarks as in the intervention group with use of prototypes and trial components.

### Study procedures

Demographic characteristics, BMI, indication for operation, type and brand of prosthesis, total amount of blood loss, surgical time, length of hospital stay and ASA classification will be collected and/or recorded for all patients included in this study.

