## Methods/Design

### Study design

A prospective clinical intervention study with use of a historical control group will be conducted. In the prospective intervention group patients will undergo rTKA using CAS. These surgeries will take place between September 2012 and September 2015. The historical control group will consist of patients who underwent rTKA between January 2002 and April 2012. The intervention and control groups will be matched according to gender and type of revision prosthesis. The study design, procedures and informed consent are approved by the Medical Ethics Committee of University Medical Center Groningen (UMCG).

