### Sample size

The hypothesis is that the use of CAS leads to fewer outliers in prosthetic alignment compared to the use of mechanical alignment guides during rTKA. Primary outcome measure will be rotational prosthetic alignment. When using the conventional operation technique, around 25% of the knees is considered a radiological outlier. Therefore, a P2 value of 0.75 was chosen [21,36]. Previous research has shown that the use of CAS in TKA decreases the number of outliers by 17-30% [21,37,38]. When a 20% decrease in outliers is expected in the CAS group compared to the control group with P1 = 0.95, P2 = 0.75, power = 80% and alpha = 0.05, 44 patients per group are needed.

Since 2008 a total of amount of 21-30 rTKAs have been performed each year at UMCG, and an increase is expected. As a result of that, the possibility is expected of including 44 patients in the intervention group between September 2012 and September 2015. Inclusion of 44 patients in the historical control group is not expected to be a problem, as 165 rTKAs were performed between January 2002 and April 2012.

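### Matching and analysis leave out the operating surgeon, so any difference in surgeon mix between the 2002-2012 controls and the 2012-2015 CAS cases would be attributed to CAS

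*Protocol article*

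**What the plan says.** The Study design section sets up an unrandomised comparison: "A prospective clinical intervention study with use of a historical control group will be conducted". The two periods do not overlap. For the CAS cases: "These surgeries will take place between September 2012 and September 2015". For the controls: "The historical control group will consist of patients who underwent rTKA between January 2002 and April 2012". Comparability rests on one sentence: "The intervention and control groups will be matched according to gender and type of revision prosthesis".

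The data list under Study procedures opens with demographics, BMI and the indication, and continues: "type and brand of prosthesis, total amount of blood loss, surgical time, length of hospital stay and ASA classification will be collected". The operating surgeon is not among the items.

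The Statistical analysis section names the Mann-Whitney U-test for alignment, and chi-square and Fisher tests for dichotomous values. It names no covariate or stratum.

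The Intervention group section has the surgeon mark the notch, the canal entry, the malleoli, the epicondyles and the two points that define tibial rotation. Of those two points it says: "Both landmarks are marked by the orthopaedic surgeon". The Historical control group section says that control components were positioned on the same landmarks, with mechanical guides and trial components. The Study population section says that anaesthesia, analgesia and physiotherapy were the same in both groups. It does not mention surgeons.

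**The concern.** The outcome is the angle at which a component was implanted, and by the article's own account that angle depends on points marked by hand. Who operated is therefore a direct rival explanation for a difference in outliers. Randomisation would have balanced it, but here there is none. Overlap in time would have helped, but the last control operation falls before the first CAS operation. Matching and adjustment are what remain, and neither is stated to use the surgeon.

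If CAS is performed mainly by surgeons whose own outlier rate is lower than that of the department as it was in 2002-2012, the comparison would show a benefit that CAS did not produce. A learning phase with CAS would push the other way and could hide a real benefit. As written, the plan could not tell either situation from a true CAS effect.

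**Working it through.** **The plan's own figure.** The Sample size section assumes non-outlier proportions of 0.95 (CAS) and 0.75 (control), 80% power and alpha 0.05, and states 44 per group. The two-sided arcsine formula gives h = 2·asin(√0.95) − 2·asin(√0.75) = 0.596 and n = 2·((1.960 + 0.842)/0.596)² ≈ 44.2. Rounded up this is 45, so 44 is reproduced to within one patient. The pooled normal formula gives 49. The present point does not depend on which was used. The 44 per group and the 25% control outlier rate are carried forward.

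**What is assumed.** The documents give no number of surgeons and no surgeon-specific rates. The following are assumptions: two classes of surgeon; CAS has no effect; all CAS cases are done by the class with the lower outlier rate; a share s of the controls is done by the other class. Then

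- CAS outlier rate = p_low
- control outlier rate = (1 − s)·p_low + s·p_high

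Three mixtures return the article's 25% for the controls:

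| p_low | p_high | s | CAS rate | Control rate |
|---|---|---|---|---|
| 15% | 35% | 0.50 | 15% | 0.5·15 + 0.5·35 = 25% |
| 10% | 40% | 0.50 | 10% | 0.5·10 + 0.5·40 = 25% |
| 10% | 30% | 0.75 | 10% | 0.25·10 + 0.75·30 = 25% |

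**Chance of a misleading result.** Take the outlier counts as independent binomials with 44 per group. Enumerate every pair of counts and sum the probabilities of those with p < 0.05 and fewer outliers under CAS:

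| CAS v control outlier rate | Uncorrected chi-square | Fisher's exact |
|---|---|---|
| 15% v 25% | 22.3% | 14% |
| 10% v 25% | 47.8% | 35% |
| 25% v 25% (same surgeon mix) | 2.7% | 1.3% |

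The last row is the right reference. A significant result *favouring CAS* is an event in one direction, so it should be set against about 2.7% (1.3% by Fisher), not against the two-sided 5%.

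The enumeration uses outlier counts because the hypothesis and the sample size are stated in outliers. The Mann-Whitney test on angles would be open to the same bias, but its size cannot be computed without angle distributions.

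**The control pool.** The article expects no difficulty in finding 44 controls, "as 165 rTKAs were performed between January 2002 and April 2012". That number counts all revisions. The NexGen requirement, the exclusions, the matching and the return visit for a CT scan all reduce it.

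**The case against.** The strongest reply has four parts.

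- **The article is condensed.** The data list is one sentence and the collection form is not shown. A reader might infer that the surgeon is not collected. The article cannot establish that, and the name can be retrieved from operation records at any time. This part stands. The point therefore rests on the matching rule and the unadjusted tests, which the article does fix; the data list only adds that the surgeon is not mentioned there either.
- **No change of surgeons is shown.** A reader might picture ten years of changing operators. The documents do not support that. This is one department with 165 revisions in just over ten years, a volume that a few surgeons could have handled throughout. The article also gives 21-30 revisions a year since 2008. Over the 4⅓ years from January 2008 to April 2012 that is about 91-130 operations, or 55-79% of the 165, so most of the pool probably comes from the years just before CAS. This stands as a limit on the likely size. It does not remove the point, because the article nowhere says that the same surgeons operated in both periods.
- **The rates are invented.** This is true. Nothing in the documents places the trial between no bias and the figures above, and Fisher's test gives smaller ones than chi-square.
- **Confounding is inherent in a declared historical-control design.** This is also true, and the surgeon is one of several unadjusted factors. But this factor acts directly on the outcome and can be addressed at little cost, so accepting the design does not mean leaving it out.

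**Conclusion.** The point holds as a conditional one. Controls are matched on gender and prosthesis type only, the comparison is unadjusted, the periods do not overlap, and the article itself makes alignment depend on the surgeon. Followed as written, the plan would attribute any difference in surgeon mix to CAS.

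If surgeon mix alone produced outlier rates of 15% v 25% or 10% v 25%, the chance of a significant result favouring CAS would be about 22% or 48% by chi-square (14% or 35% by Fisher), instead of about 2.7% (1.3%). With the same mix in both groups the bias is nil. These figures rest on assumed surgeon rates and shares, full concentration of CAS in the lower-rate class, and no CAS effect.

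The documents do not support the stronger conclusion that surgeons did differ, or that an observed CAS benefit would be spurious. The direction is open too, since a learning phase would work against CAS. This is a worthwhile, inexpensive improvement to the design and analysis, not an error or a contradiction in the article.

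**What to change.** 1. **Study procedures:** take the operating surgeon from the operation records for both groups, and report a surgeon-by-group table. If the same surgeons operated in similar shares, the table shows it and strengthens the sponsor's conclusion.
2. **Study design:** where the matched pool allows, choose controls first from operations by surgeons who also perform the CAS cases, and use others only when no such match exists.
3. **Statistical analysis:** add a sensitivity analysis of outliers stratified by surgeon (Mantel-Haenszel). It draws only on surgeons who appear in both groups, so state how many patients contribute.
4. **Conclusion:** if few surgeons appear in both groups, stratification cannot separate the two explanations. Word the result as a comparison of technique and operator combined.
5. **Learning:** each surgeon's CAS sequence number may be used to describe a learning effect. It exists only for CAS cases, so it cannot adjust the comparison between groups.

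The cost is one field extracted from existing records, one table and one extra analysis, with no additional patients. The downsides are fewer first-choice controls, since the eligible pool is smaller than 165, and wider intervals when strata are small.

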### Radiographic evaluation

Rotational prosthetic alignment will be measured on a CT-scan of the operated leg. For evaluation of alignment in the coronal and sagittal planes a new imaging device, called the EOS system (Biospace Imaging, Paris, France) [28], will be used. This device is characterized by a reduction in radiation (800-1000 times less than for CT-scan and 10 times less than conventional X-ray) [28,29]. Reason for this is the use of an innovative technology called fast gaseous particle detectors, invented by George Charpak (which earned him the Nobel prize in physics in 1992). The EOS imaging device uses two orthogonal sources of radiation and linear detectors that are coupled together. These sources move up and down along the patient, producing an anterior-posterior and lateral image at the same time while the patient is in weightbearing position. This is a different technique than conventional radiograph systems, where beams are divergent in horizontal and vertical plane.

Of the patients in the intervention group, a CT-scan of the operated leg will be made postoperatively during the visits at the outpatient clinic. Patients included in the historical control group have already undergone the standard surgical technique for rTKA. A CT-scan of the operated leg will be made the next time the patient visits the outpatient clinic of the Orthopedic Department for follow-up of the rTKA.

For evaluation of rotational prosthetic alignment, rotation of the femoral and tibial components will be determined separately according to the Berger CT protocol [30]. Angles measured for rotational alignment are:

– Condylar twist angle for rotation of the femoral component: angle between the epicondylar axis and the prosthetic posterior condylar axis (inner border of posterior cut). Endorotation of the femoral component will be shown as a positive (+) angle and exorotation of the femoral component will be shown as a negative (-) angle. An angle of >3° endorotation or exorotation will be considered an outlier.

– Rotation of the tibial component: angle between the tibial tubercle axis (axis between the geometric center of the proximal tibial plateau and the tip of the tubercle) and the tibial component angle (anterior-posterior line through the tibial component). Normal rotation of the tibial component is considered 18° endorotation [30]. Endorotation of the tibial component will be shown as a positive (+) angle and exorotation of the tibial component will be shown as a negative (-) angle. An angle of >3° endorotation or exorotation will be considered an outlier.

Prosthetic alignment in the coronal and sagittal planes will be measured using postoperative coronal and sagittal X-rays of the operated leg. These lower-limb X-rays are obtained using the EOS system (Biospace Imaging, Paris, France) [28] EOS 2D images will be used for measuring alignment. For the intervention group, standard coronal and sagittal X-rays will be taken postoperatively as part of the standard operation protocol. For the historical control group, standard coronal and sagittal X-rays have already been taken postoperatively.

Angles measured for coronal and sagittal alignment are:

– Mechanical angle of the leg (HKA): Angle between the line from the femoral head to the center of the knee and the line from the center of the ankle to the center of the knee in coronal plane.

– Mechanical lateral distal-femoral angle (mLDFA): Angle between the mechanical axis of the femur and the articular surface of the femoral part of the prosthesis in coronal plane.

– Mechanical medial proximal tibial angle (mMPTA): Angle between the mechanical axis of the tibia and the articular surface of the tibial part of the prosthesis in coronal plane.

– Anatomical proximal posterior tibial angle (aPPTA): Angle between the mechanical axis of the tibia and the articular surface of the tibial part of the prosthesis in sagittal plane. Downslope of the design of Nexgen prostheses is 7°, and this angle is considered the normal aPPTA.

– For the mechanical axis of the leg, mLDFA, mMPTA and aPPTA a generally accepted outlier cut-off of +/-3° will be applied in this study [31-34].

The canal-filling ratio (CFR) will be determined in both the intervention and control groups to assess whether the stems are canal-filling. The CFR will be measured on the coronal and sagittal EOS images as described by Parsley et al. [35]. The stem diameter and endosteal diameter will be measured at the stem tip. The CFR will be calculated by dividing the stem diameter by the endosteal diameter. A stem is considered to be canal-filling when the CFR is ≥0.85 [35].

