## Background

Osteoarthritis (OA) is one of the most prevalent age-related musculoskeletal conditions. Although OA may affect any joint of the body, it is most commonly seen in the hip and knee [1]. OA of the knee leads to a significant impairment in patients’ ability to perform activities of daily living and has a large impact on health-related quality of life [2,3]. For advanced OA of the knee, total knee arthroplasty (TKA) is a highly successful and widely applied surgical treatment, with 450,000 primary TKAs performed in the United States in 2005 [4] and 21,475 TKAs in the Netherlands in 2010 [5]. Due to a growing elderly population and changing thresholds for surgery, these numbers are expected to increase dramatically in the coming decades [4,6].

As a result, the number of TKA revisions (rTKA) will also increase. The demand for rTKA is expected to double by 2015 and a growth of 601% is predicted for the United States between 2005 and 2030 [7]. A similar trend is expected for other Western countries. Main reason for rTKA is aseptic loosening, which accounts for 30-42% of all rTKAs. Infection is the second most common indication and is responsible for about 20% of all revisions. Other reasons for rTKA may be pain, instability, wear, fracture, malalignment, implant breakage, incorrect size and dislocation of one or more components [8,9]. Main reasons for rerevision after rTKA are infection (35-46%), followed by aseptic loosening (19-30%). Other reasons for rerevision are wear/osteolysis, instability, stiffness and periprosthetic fractures [10,11].

The goal of both primary and revision TKA is to restore function and stability of the knee joint and to alleviate pain. However, rTKA is a more complicated surgical procedure than primary TKA and leads to worse clinical results. Major differences between revision and primary TKA are the amount of bone loss and ligamental damage [12,13]. Reasons for this are osteolytic lesions caused by wear, aseptic loosening or infection, and removal of the primary implant.

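### Rotation, the primary outcome, is scanned at postoperative visits in CAS knees but about four months to over ten years after surgery in controls, so later component movement would be read mainly in controls as position at implantation

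*Protocol article*

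**What the plan says.** The Sample size section states: "Primary outcome measure will be rotational prosthetic alignment". Under Radiographic evaluation, rotation is measured on a CT of the operated leg. On timing, that section says of the intervention group that "a CT-scan of the operated leg will be made postoperatively during the visits at the outpatient clinic", and of the controls: "A CT-scan of the operated leg will be made the next time the patient visits the outpatient clinic of the Orthopedic Department". Neither statement sets an interval from surgery.

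The surgery dates come from Study design. For controls: "The historical control group will consist of patients who underwent rTKA between January 2002 and April 2012". For CAS: "These surgeries will take place between September 2012 and September 2015". The same section adds: "The intervention and control groups will be matched according to gender and type of revision prosthesis". The surgery-to-CT interval is not a matching factor.

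The outlier rule is applied to a single CT angle: "An angle of >3° endorotation or exorotation will be considered an outlier". For the coronal and sagittal planes, the article says the controls' postoperative films already exist. The delayed measurement therefore concerns the CT outcome.

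**The concern.** The objective is the effect of the surgical technique on alignment, that is, where the technique puts the component. A CT shows where the component is on the day of the scan. The two are the same only if nothing has moved in between.

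Here the time available for movement follows group membership. Controls can have had many years. CAS knees are scanned at postoperative visits. With one CT per control and no early CT to compare it with, a component that rotated after surgery cannot be told from one implanted in that position, and it would count against the mechanical guide. The cut-off is only 3°, so modest movement can change the classification. The primary comparison could then mix surgical accuracy with later stability of the implant, probably in the direction of the hypothesis.

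**Working it through.** **1. The plan's own figure.** The Sample size section gives 44 per group for 95% against 75% non-outliers, 80% power and alpha 0.05. The two-sided arcsine formula reproduces it: h = 2[asin(√0.95) − asin(√0.75)] = 0.596, and n = 2(1.960 + 0.842)²/0.596² = 44.2. This point does not change the sample size.

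**2. Interval from surgery to CT in controls.** The article gives no start date for control scans. I assume September 2012, when CAS surgery starts.
- Surgery at the end of April 2012: about 4 months.
- Surgery in January 2002: 10.7 years.
- Surgery in January 2002 with the scan as late as September 2015: 13.7 years.

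**3. Effect on an outlier comparison.** The article gives a 25% outlier rate for the conventional technique. Set placement equal in both groups at 25%, so there is no CAS effect. Let m be the share of in-range controls that have moved beyond 3° by the scan. The documents give no value for m; 5%, 10% and 15% are assumptions.
- No movement back into range: control rate = 25% + 75% × m.
- Outliers also move back at rate m: control rate = 25% + 75% × m − 25% × m = 25% + 50% × m.

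Exact rejection probabilities of the uncorrected two-sided chi-square test, 44 per group, CAS rate 25%:

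| m | Control rate, no return | Rejects | Control rate, equal return | Rejects |
|---|---|---|---|---|
| 0 | 25.0% | 5.3% | 25.0% | 5.3% |
| 5% | 28.8% | 7.1% | 27.5% | 6.1% |
| 10% | 32.5% | 12.6% | 30.0% | 8.5% |
| 15% | 36.3% | 21.6% | 32.5% | 12.6% |

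At m = 2% without return the figure is 5.6%, which is negligible. Fisher's exact test, also named for dichotomous values, is more conservative: 2.6%, 3.9%, 7.8% and 14.9% for m = 0, 5%, 10% and 15% without return. A lower base rate makes the effect larger: at 15% the chi-square rejects in 8.7%, 17.9% and 32.0% for m = 5%, 10% and 15%.

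**4. Effect on the test named for alignment.** The Statistical analysis section assigns the Mann-Whitney test to rotational alignment, and the angles are signed. I simulated 44 per group with normal deviations from target and 25% beyond ±3° (SD = 3/1.150 = 2.61°). The same share m of in-range controls was moved to between 3° and 6° (assumption).
- Movement in random directions: about 5% for all three values of m. The distribution widens but its centre stays, and the test responds mainly to a shift.
- All movement in one direction: about 6%, 9% and 13% for m = 5%, 10% and 15%.

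**The case against.** Several objections have force.

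- **The migration rate has no anchor.** The Background attributes 19-30% of re-revisions after rTKA to aseptic loosening. A reader might take this as the share of control components that have moved. It is a share of re-revisions, and those components were replaced. It gives no prevalence of unrevised components rotated beyond 3°. It shows only that late loss of fixation is a recognised event.
- **Direction is not certain.** Movement can bring an outlier back into range, and CAS knees can move before their scan. Controls who loosened and were re-revised or stopped attending may be missing, which would flatter the control group. Because outliers are the minority at a 25% base rate, equal movement each way still adds outliers on balance. Hence likely, not certain.
- **CAS scans are not stated to be early.** The article says only that they are made at postoperative visits. That they come sooner is a fair inference, not a stated fact.
- **Ten years is the tail.** At 21-30 operations a year since 2008, the 4⅓ years from January 2008 to April 2012 supply about 91-130 of the 165 available controls (55-79%), all less than five years before September 2012.
- **The interval can be computed later** from operation and scan dates, and an analysis of it could sit in an analysis plan that is not shown. This is true, but the unequal timing is fixed in the article itself, and no later analysis can supply an early control CT.

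These points limit the size of the problem. They do not remove the link between group and time to scan.

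**Conclusion.** The point holds as a structural weakness of the primary outcome. The surgery-to-CT interval follows group membership, and the described design cannot separate position at implantation from later rotation in controls. The likely net effect is extra control outliers, of unknown size.

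Under an assumed 5-15% of in-range controls moving out of range, no CAS effect and a 25% base rate, a chi-square on outliers rejects in 7-22% of trials without movement back and in 6-13% with equal movement back. The Mann-Whitney test on signed angles stays near 5% for random-direction movement and reaches about 6-13% for one-way movement.

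A reader might infer that migration is known to inflate the control outlier rate, or that the false-positive rate is 7-22% whatever the test. The documents support neither: they give no migration rate, and they name the Mann-Whitney test for alignment. What they support is a limit on what a late control CT can show about surgical placement.

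**What to change.** 1. Name one postoperative outpatient visit for the CAS CT.
2. Record the surgery-to-CT interval for every knee in both groups.
3. Pre-specify control rotation and outlier rate by interval, with the group comparison repeated in controls with shorter intervals.
4. Pre-specify a sensitivity analysis that excludes, in both groups, only components whose position has demonstrably changed between the first postoperative films and later routine films. Do not exclude on loosening alone. The Discussion links coronal and sagittal malalignment to loosening, so that rule could remove components that were badly placed at surgery and make the control group look better than it was.
5. State that the CT result reflects position at the time of scanning, and limit the claim about surgical placement if these analyses disagree with the primary one.

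**Cost.** No extra scans and no change to the sample size; one recorded item per knee, a comparison of films on file, and two additional analyses. The comparison assumes that later routine films exist, which the article does not state. The sensitivity analyses have smaller numbers, pure rotational movement is only partly visible on films, and the interval is partly confounded with calendar era, so a trend by interval would not prove migration.
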